### Laboratory analyses

The blood samples obtained at the three study visits will be analysed using a panel of platelet function and biomarker tests in a central laboratory. All laboratory tests will be performed in accordance with reagent manufacturers’ instructions and with locally generated standard operating procedures. The following analyses will be performed:(i)Light transmission aggregation (LTA) in platelet-rich plasma (PRP) in response to stimulation with collagen-related peptide (CRP), adenosine diphosphate (ADP), arachidonic acid (AA), thromboxane receptor agonist (U46619) and thrombin-related activator peptide 6 (TRAP 6).(ii)Flow cytometry to quantify surface CD62P expression and PAC-1 binding in unstimulated platelets and in platelets stimulated with CRP and TRAP 6.(iii)Adhesion and aggregation of platelets in whole blood on a collagen surface under flow conditions.(iv)Plasma concentrations of soluble CD40 ligand (sCD40L) and thromboxane B2 (TXB2) to assess baseline in vivo platelet activation and thromboxane A2 biosynthesis respectively. These biomarkers will be measured by enzyme-linked immunosorbent assay using frozen plasma samples, after the end of recruitment.

### Primary outcome

The primary outcome is the maximum amplitude of the LTA response to TRAP 6 expressed as a percentage of the absolute difference in light transmission between PRP and platelet-poor plasma. This was selected as the primary outcome since the functional response to TRAP 6 represents the best marker of the overall extent of platelet inhibition.

### Secondary outcomes

The secondary outcomes will be the following laboratory test results:(i)Maximum amplitude of the LTA responses to CRP, ADP, AA and U46619.(ii)Median fluorescence intensity of anti-P selectin and PAC-1 binding to platelets in unstimulated platelets and after stimulation with CRP and with TRAP 6.(iii)Aggregation and adhesion parameters of platelets exposed to a collagen surface under flow conditions.(iv)Plasma concentrations of sCD40L and TXB2.

### Sample size

The sample size has been set at 110 patients, which is sufficient to detect a standardised difference in the primary outcome between the two study interventions of 0.35 standard deviations. The sample size has been calculated with the following assumptions:Correlation between the primary outcome measured at visit 1 and at visit 2 = 0.5No cross-over anticipated10% loss to follow-up (i.e. missing outcome data at visit 2)

DAPT with ASP + any P2Y_12_ blocker is prescribed as part of standard current care at the BHI to approximately 1500 adults per year who undergo PCI and coronary stent insertion. We estimate that approximately 1200 (80%) will complete the prescribed duration of treatment of 6–12 months. Based on previous observational studies at the BHI, we conservatively estimate that the overall recruitment and completion rate will be approximately 10% of eligible patients. Therefore, we predict that 110 patients will occur in 14–16 months.

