**Methods:**

To compare TIC with TIC + ASP, we have initiated a single centre, open-label randomised controlled trial (TEMPLATE study) in adults receiving DAPT following PCI with a sample size of 110 patients. Patients are invited to join the study when, as part of standard care, they are due to switch from DAPT (ASP + any P2Y_12_ blocker) to single antiplatelet treatment with ASP alone after 6–12 months. Patients are randomised to receive either TIC or TIC + ASP for 4 weeks. All patients then revert to standard care with ASP alone. Blood samples and clinical data are collected at three study visits: at baseline during treatment with ASP + any P2Y_12_ blocker (visit 1); approximately 4 weeks after visit 1 during treatment with either TIC or TIC + ASP (visit 2); and approximately 8 weeks after visit 1 when treatment has reverted to ASP alone (visit 3). The primary outcome is the extent of platelet inhibition, measured by light transmission aggregation, flow cytometry, flow chamber and plasma biomarker tests. The primary analysis will compare the extent of platelet inhibition between the TIC and TIC + ASP groups at visit 2, adjusted for baseline platelet reactivity. Secondary analyses will compare the extent of platelet inhibition at visit 2 with that at visit 3.

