### Randomisation

Allocation to the TIC + ASP group or the TIC group in a 1:1 ratio will be performed by an authorised member of the research team using a secure internet-based randomisation system (http://www.sealedenvelope.com/), using block randomisation with blocks of varying sizes. Clinicians, research nurses, trial coordinators, pharmacists and patients will be aware of the allocation. As the trial is open label, no code-breaking procedure is required. Since the costs associated with production of a placebo medication were prohibitively high, we adopted a pragmatic open-label design in which the study patients, their clinicians, research nurse and trials coordinator will not be blinded to treatment allocation. We do not anticipate this to have a significant impact on trial results. The laboratory staff will be blinded to group allocation.

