### Statistical analysis

The laboratory test results will be expressed as continuous variables. The results for the primary comparison of the maximum amplitude of the LTA response to TRAP 6 between the TIC + ASP and TIC groups will be analysed using linear mixed regression. The baseline (visit 1) and post-intervention values (visit 2) will be modelled jointly in preference to the pre-randomisation value being modelled as a covariate to avoid the necessity either to exclude cases with missing pre-intervention measures or to impute missing pre-intervention values. The secondary outcome measures will be compared similarly.

The study will also enable the extent of platelet inhibition to be described within subjects over time as their treatment changes (i.e. from visit 1 to visit 2 to visit 3).

Comparative analyses will be on the basis of intention to treat and mean differences will be quantified with 95% confidence intervals. The width of the individual confidence intervals for the secondary outcomes will be adjusted for the number of tests carried out (Bonferroni correction).

The primary analysis will take place when follow-up and laboratory analyses are complete for all recruited patients. No interim or subgroup analyses are planned other than those outlined above. Safety data will be reviewed regularly by the trial management group who meet at frequent intervals to discuss trial progress. During these meetings the rate of adverse events in the study population will be monitored against the anticipated rate of events that are expected for the target population.

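### The sample-size claim is wrong: 110 patients in total give about 51% power for a 0.35 SD difference, and 110 is close to the number needed per arm

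*Protocol article*

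**What the plan says.** The Sample size section of the protocol article states: "The sample size has been set at 110 patients". It calls this number "sufficient to detect a standardised difference in the primary outcome between the two study interventions of 0.35 standard deviations". The assumptions follow the words "The sample size has been calculated with the following assumptions": a correlation of 0.5 between the primary outcome at visits 1 and 2, no cross-over, and 10% without outcome data at visit 2. Neither a significance level nor a power is given.

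The number 110 is the whole trial, not one arm. The abstract describes a trial "in adults receiving DAPT following PCI with a sample size of 110 patients", and the recruitment forecast says "we predict that 110 patients will occur in 14–16 months". The Randomisation section specifies "Allocation to the TIC + ASP group or the TIC group in a 1:1 ratio".

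For the analysis, the Statistical analysis section says "The baseline (visit 1) and post-intervention values (visit 2) will be modelled jointly", and that "mean differences will be quantified with 95% confidence intervals".

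**The concern.** The section lists its assumptions and then asserts that the trial can detect a difference of a given size. Those assumptions are enough to test the assertion, and about 50 evaluable patients per arm looks too few for 0.35 SD even after a baseline correlation of 0.5 is credited.

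This is the only quantitative justification of the trial's size, and it concerns the primary outcome. If it is wrong, a true difference of the stated size could easily be missed. The Discussion makes this more serious: it says that a result showing no difference between the groups would support avoiding aspirin. A reader who trusts the Sample size section would give such a result more weight than it can carry.

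**Working it through.** **Inputs**
- Total N = 110, difference 0.35 SD, correlation r = 0.5, loss 10%, no cross-over (Sample size).
- 1:1 allocation (Randomisation).
- Visits 1 and 2 modelled jointly (Statistical analysis). I take the favourable reading, that this is as efficient as adjusting for baseline as a covariate, so the residual variance is 1 − r² = 1 − 0.25 = 0.75 in units of SD².
- Two-sided 5%: an assumption, consistent with the planned 95% confidence intervals.
- Power of 80% or 90%: assumptions, as the usual design targets.

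**Attempt to reproduce the stated figure with 110 as the total**
- Evaluable: 110 × 0.9 = 99, or 49.5 per arm.
- SE = √(0.75 × 2 / 49.5) = 0.174 SD.
- Detectable difference at 80% power: (1.96 + 0.84) × 0.174 = 0.49 SD.
- Detectable difference at 90% power: (1.96 + 1.28) × 0.174 = 0.56 SD.
- Power for 0.35 SD: 0.35 / 0.174 = 2.01, and Φ(2.01 − 1.96) = 52.0%. The noncentral t gives 51.2%, and a 20,000-run simulation of the baseline-adjusted analysis gives 51.0%.

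The stated figure is not reproduced. The true detectable difference is larger than stated by 0.49 / 0.35 = 1.4 times (80% power) to 0.56 / 0.35 = 1.6 times (90% power).

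**Number needed for 0.35 SD**
- 80% power: 2 × 0.75 × (2.80 / 0.35)² = 96.1, so 97 evaluable per arm. After loss, 97 / 0.9 = 107.8, so 108 per arm and 216 in total.
- 90% power: 129 evaluable per arm, 287 in total after loss.
- Reading 110 as per arm: 99 evaluable per arm, SE = √(0.75 × 2 / 99) = 0.123, detectable difference 0.345 SD at 80% power, and 81% power for 0.35 SD.

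**Can another reading rescue 110 as the total?** Power for 0.35 SD (normal approximation):

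| Variant | Power |
|---|---|
| Two-sided 5%, 10% loss | 52% |
| Two-sided 5%, no loss | 56% |
| One-sided 5%, 10% loss | 64% |
| One-sided 5%, no loss | 68% |
| Change scores, two-sided 5%, 10% loss | 41% |

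Reaching 80% with 99 evaluable patients would need a residual variance of (0.35 / 2.80)² × 49.5 / 2 = 0.39, that is a correlation of √(1 − 0.39) ≈ 0.78 instead of 0.5. A one-sided 10% test with no loss at all gets to about 80%, but this contradicts the stated 10% loss and does not match 95% intervals. Visit 3 cannot help, because by then every patient is on aspirin alone.

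**The case against.** The strongest counter-argument concerns where the number came from. The match with 108 per arm is suggestive but not conclusive, because 110 as a total also fits a different reading. The expected half-width of the 95% confidence interval is 1.96 × 0.174 = 0.341 SD, or 0.346 SD with the t distribution, which is close to 0.35. Both readings fit because (1.96 + 0.84)² ≈ 7.85 is nearly 2 × 1.96² ≈ 7.68. So 0.35 may have been a precision figure, or may simply be misstated. This stands: the per-arm origin is one plausible explanation, and the document does not confirm it. It does not save the sentence, because the section speaks of detecting a difference. Designing to the half-width amounts to about 50% power, which is not a usual target.

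A second point is that what a null result excludes depends on its confidence interval, not on planned power, and the plan does commit to reporting that interval. This also stands, but helps little. With a half-width of 0.341, the interval excludes a 0.35 SD advantage of dual therapy only if the estimate in that direction is below about 0.35 − 0.341 = 0.009 SD.

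Third, alpha and power are not stated, and in a condensed article that is not a fault in itself. The 51% is therefore conditional on two-sided 5%. The conclusion is not: no usual combination of level and power makes the claim true under the listed assumptions.

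**Conclusion.** The concern holds. A total of 110 patients and a detectable difference of 0.35 SD are incompatible under the protocol's own assumptions. Power for 0.35 SD is about 51%, so a true difference of that size would be missed about half the time.

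The 51% rests on a two-sided 5% level, 1:1 allocation, 99 evaluable patients and full efficiency from baseline adjustment. The last is generous: if the joint model in effect compares changes from baseline, power falls to 41%. Dropping the loss and moving to a one-sided 5% test together raise it only to 68%.

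The document does not show which number is in error. A per-arm requirement used as the total is the closest match at a conventional power.

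**What to change.** State alpha and power, and make the number of patients and the detectable difference agree. The minimum correction keeps N and changes the claim, for example: 110 patients (about 99 evaluable, correlation 0.5, two-sided 5%) give 80% power to detect 0.49 SD and 90% power to detect 0.56 SD; power for 0.35 SD is about 51%; the expected half-width of the 95% confidence interval is about 0.34 SD. The same figures should go into the SAP. The cost is one paragraph and a less favourable stated detectable difference, with no extra patients.

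The sponsor should also confirm which figure was intended. If 0.35 SD is the difference the trial has to detect, the total is what needs correcting: about 216 patients for 80% power, which is 106 more. At the forecast pace of 110 in 14–16 months, that is 216 / 110 × 14 to 216 / 110 × 16, or roughly 27 to 31 months. The Study status section says recruitment was still open at publication, so this choice was still available then.

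In either case, the Discussion should tie any conclusion of no difference to the confidence interval obtained, not to the 0.35 SD figure.

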### Statistical analysis

The laboratory test results will be expressed as continuous variables. The results for the primary comparison of the maximum amplitude of the LTA response to TRAP 6 between the TIC + ASP and TIC groups will be analysed using linear mixed regression. The baseline (visit 1) and post-intervention values (visit 2) will be modelled jointly in preference to the pre-randomisation value being modelled as a covariate to avoid the necessity either to exclude cases with missing pre-intervention measures or to impute missing pre-intervention values. The secondary outcome measures will be compared similarly.

The study will also enable the extent of platelet inhibition to be described within subjects over time as their treatment changes (i.e. from visit 1 to visit 2 to visit 3).

Comparative analyses will be on the basis of intention to treat and mean differences will be quantified with 95% confidence intervals. The width of the individual confidence intervals for the secondary outcomes will be adjusted for the number of tests carried out (Bonferroni correction).

The primary analysis will take place when follow-up and laboratory analyses are complete for all recruited patients. No interim or subgroup analyses are planned other than those outlined above. Safety data will be reviewed regularly by the trial management group who meet at frequent intervals to discuss trial progress. During these meetings the rate of adverse events in the study population will be monitored against the anticipated rate of events that are expected for the target population.

### Research approval

Research ethics approval and clinical trial authorisation were granted in October 2014 by the South-Central Oxford A Research Ethics Committee (reference 14/SC/1309) and the Medicines and Healthcare Regulatory Agency (EUDRACT No. 2013-002734-20) respectively. The trial is managed by the Clinical Trials and Evaluation Unit Bristol (CTEU Bristol) and sponsored by the University Hospitals Bristol NHS Foundation Trust (www.uhbristol.nhs.uk/research-innovation/). Trial governance is through the sponsor’s standard operating procedures. The trial is registered as ISRCTN84335288 and conforms to SPIRIT guidelines (see Fig. 2 and Additional file 1: SPIRIT checklist).

### Changes to the protocol since first approved

There have been three substantial amendments made to the protocol since it was first approved. The first amendment was approved in May 2015 and incorporated minor clarifications in addition to the new recommendations from the European Society of Cardiologists. These recommendations led to a change in duration of standard DAPT specified in the protocol, from 12 months to between 6 and 12 months after PCI and insertion of a drug-eluting stent; this change increased the pool of eligible patients.

The second amendment to the protocol was approved in August 2015, removing the plan to establish a Data Monitoring and Safety Committee (DMSC). This change was made because, on review of the study design, it became apparent that the study would not benefit from a DMSC. Instead, the safety data are being reviewed closely by the trial management group and the Steering Committee for Cardiovascular Studies, a subgroup of the University Hospitals Bristol NHS Foundation Trust Cardiovascular Research Board.

The third amendment was approved in September 2016. This amendment widened the inclusion criteria from receiving ASP + CLOP for 6–12 months to receiving ASP + any P2Y_12_ blocker for 6–12 months. This widening of the inclusion criteria was made to enhance study enrolment because shortly after starting the study, the institutional standard care changed from using CLOP as the preferred P2Y_12_ blocker, to other P2Y_12_ blockers for some patient subgroups. After this amendment, the enrolment rate increased to that predicted in the original study design.

## Discussion

The TEMPLATE study design will enable unbiased comparison of the effects of TIC versus TIC + ASP on platelet activity in patients with coronary artery disease. It will also enable a longitudinal comparison of the effects TIC and TIC + ASP with the effects of ASP alone in the same patients. The laboratory tests selected for this study will enable measurement of functional platelet responses to a panel of activating agonists using LTA, flow cytometry and flow chamber tests, selected to measure the extent of inhibition of the multiple platelet activation pathways. We will also measure the extent of baseline platelet activity by testing unstimulated platelets by flow cytometry and with the soluble platelet activation biomarker tests. Together, these data will provide a comprehensive description of the overall pharmacodynamic effects of the different antiplatelet treatments. This information has not been reported previously in cohorts of patients with coronary artery disease receiving TIC or TIC + ASP. To our knowledge, there are no similar previous studies in this patient group that have evaluated the pharmacodynamic effect of monotherapy with other P2Y_12_ blockers, including CLOP.

The TEMPLATE study design allows the information to be obtained in a low-risk setting. We are enrolling patients at the point in the standard clinical care pathway when there is a transition from DAPT to single-antiplatelet treatment with ASP, typically at 6 to 12 months after the PCI procedure. This is after the interval of greatest risk of major adverse cardiac events and abnormal bleeding following PCI [12]. Furthermore, the duration of exposure to the study treatment (i.e. either TIC or TIC + ASP) is only 4 weeks, which will minimise the likelihood of adverse events attributable to the study drugs. The short overall study participation of 8 weeks during which there are only three study visits should facilitate study delivery and minimise patient drop-out.

The main benefit of the TEMPLATE study is that the findings will provide evidence to either support or refute the hypothesis that TIC monotherapy enables platelet inhibition to the same extent as dual therapy with TIC + ASP. This is significant clinically because abnormal bleeding is a major complication of all antiplatelet therapy, but particularly of ASP which adversely affects gastric mucosa, increasing the risk of gastrointestinal bleeding [9]. If the findings of the TEMPLATE study indicate no difference in platelet inhibition between the TIC treatment group and the TIC + ASP treatment group, then this would support avoidance of ASP in this patient group, potentially conferring a safety advantage. This is also part of the rationale of the large-scale GLOBAL LEADERS randomised controlled trail (NCT01813435) of 16,000 participants in which the study group receive TIC + ASP for 1 month after PCI and coronary stent insertion followed by TIC monotherapy for a further 23 months. The control group is DAPT with TIC + ASP or CLOP + ASP for 12 months [10]. The outcomes of the GLOBAL LEADERS study are all-cause mortality or non-fatal new Q-wave myocardial infarction (composite primary outcome) and bleeding (secondary outcome), but do not include pharmacodynamic measures of the effect of the different antiplatelet regimes. We anticipate that reporting of TEMPLATE study results in a peer-reviewed publication will precede reporting of the GLOBAL LEADERS study results and that our results will assist interpretation and help inform future treatment guidelines.

### Study status

The trial opened to recruitment in December 2015 with the first patient recruited in January 2016. Recruitment is ongoing.

## Abbreviations

AA: Arachidonic acid (a platelet metabolite that stimulates platelets in vivo and is also used as a laboratory reagent to study platelet activation responses)
ACS: Acute coronary syndrome
ADP: Adenosine diphosphate (a P2Y_12_ receptor agonist that stimulates platelets in vivo and is also used as a laboratory reagent to study platelet activation responses)
ASP: Aspirin
BARC: Bleeding Academic Research Consortium
BHI: Bristol Heart Institute
CABG: Coronary artery bypass grafting
CLOP: Clopidogrel
CTEU Bristol: Clinical Trials and Evaluation Unit Bristol
CRP: Collagen-related peptide (a platelet activating chemical that is used as a laboratory reagent to study platelet activation responses)
DAPT: Dual antiplatelet therapy
DMSC: Data monitoring and safety committee
LTA: Light transmission aggregation
NHS: National Health Service
NIHR: National Institute for Health Research
P2Y_12_: P2Y purinoreceptor 12
PCI: Percutaneous coronary intervention
PRP: Platelet-rich plasma
sCD40L: soluble CD40 ligand (a soluble plasma biomarker of platelet activation in vivo)
TXB2: Thromboxane B2 (a soluble plasma biomarker of platelet activation)
TIC: Ticagrelor
TRAP 6: Thrombin receptor agonist peptide-6 (a platelet PAR1 receptor agonist that is used as a laboratory reagent to study platelet activation responses)
U46619: A thromboxane receptor agonist that is used as a laboratory reagent to study platelet activation responses
